### 2.10. Statistical Analysis

For baseline variables, bivariate relationships will be examined by employing McNemar’s test for categorical variables and paired samples *t*-tests or Wilcoxon signed-rank test for continuous variables, presented as either means with standard deviations or medians with interquartile ranges, depending on their distribution. The primary outcome will be analyzed comparatively between the single-lead monitoring group and the control arm using McNemar’s test for paired binary outcomes. Effect sizes will be presented as risk differences with corresponding 95% confidence intervals, derived from the discordant pairs. This approach directly reflects the open-label paired design of the trial.

During the 12-month observation period, Kaplan–Meier curves will be generated for each arm and compared using a log-rank test to evaluate potential differences. The Statistical Package for the Social Sciences (SPSS version 26.0, IBM SPSS Statistics, Armonk, New York, NY, USA) will be employed for statistical analyses. A *p*-value < 0.05 is deemed statistically significant.

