This study aims to evaluate the efficacy of AF detection using a single-lead patch compared to conventional 24 h Holter monitoring in stroke patients identified with ESUS. Additionally, we aim to explore the detection rates of incidental AF in patients exhibiting LA enlargement or elevated NT-proBNP levels, providing potential indicators of AF in patients with non-cardioembolic stroke, including those due to large-artery atherosclerosis (LAA) and small-vessel occlusion (SVO).

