### 2.4. Study Population

Nine hospitals in South Korea participated in this trial: Eunpyeong St. Mary’s Hospital, the Catholic University of Korea, Kangdong Sacred Heart Hospital, Gachon University Gil Medical Center, Hanyang University Myongji Hospital, SMG–SNU Boramae Medical Center, Soon Chun Hyang University Hospital Bucheon, Inje University Sanggye Paik Hospital, and Chosun University Hospital. Each institution is equipped with a dedicated stroke unit and the necessary monitoring and imaging facilities to provide standardized stroke care by experienced specialists.

The absence of diagnosed AF at admission, confirmed through baseline surface ECG, is the key criterion. Eligible participants are as follows: (1) age over 18 years, (2) non-lacunar infarction or non-atherosclerotic cerebral infarction without corresponding artery stenosis > 50% (less than 6 months after stroke onset), (3) no history of AF and showing no AF during initial monitoring, (4) at least 18 h of recording on 24 h Holter monitoring, (5) at least 72 h of recording on a single-lead wearable patch, and (6) who underwent MRI and TTE examination. Subjects were excluded if they (1) exhibited AF on baseline ECG, (2) had valvular heart diseases (e.g., rheumatic mitral stenosis, a mechanical or bioprosthetic heart valve, or mitral valve repair, infective endocarditis), (3) had underlying disease related to AF (recent cardiothoracic and noncardiac surgery (<2 weeks), recent ST-elevation myocardial infarction (MI) (<3 months), pericarditis, myocarditis, hyperthyroidism, electrocution, pneumonia, and pulmonary embolism), (4) had implanted pacemakers, (5) suffered from advanced systemic disease or coexisting neurological/psychiatric conditions, (6) had contact dermatitis or other skin disorders, (7) lacked data on transesophageal echocardiography, or (8) were unable to participate in the study due to other causes.

According to the TOAST classification system, large artery atherosclerosis is defined as corresponding artery stenosis > 50% and small-vessel disease as a subcortical lesion < 15 mm. Patients whose index stroke was LAA or SAO were included if they exhibited LA enlargement.

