### 2.7. Concomitant Application

At baseline, upon enrollment, AF detection rates are concurrently compared using a single-lead wearable patch and a 24 h Holter monitor, with observations spanning 48 h. The Holter monitor is used for 24 h (at least 18 h), whereas the single-lead wearable patch is applied for 5 days (at least 72 h). Patients with ESUS will undergo follow-up assessments using both the single-lead patch and the 24 h Holter monitor at enrollment (visit 0) and at 6 months (visit 1).

In the context of clinical AF, this study follows a specific definition: AF is identified when an ECG recording captures an episode lasting 30 s or longer. This definition aligns with the criteria established in the 2020 European Society of Cardiology guidelines for the diagnosis and management of AF [6].

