Two large international randomized clinical trials—NAVIGATE ESUS and RESPECT ESUS—evaluated the efficacy of NOACs (rivaroxaban and dabigatran, respectively) compared to aspirin in patients with ESUS. However, both trials failed to demonstrate a benefit of NOACs over aspirin in preventing recurrent ischemic stroke [8,9]. Furthermore, the ATTICUS trial, which evaluated apixaban, was prematurely terminated following an interim analysis due to lack of efficacy [25]. Initially, it was hypothesized that covert AF frequently underlies ESUS and that NOACs might therefore be beneficial for secondary prevention. However, the lack of efficacy observed in the NAVIGATE ESUS and RESPECT ESUS trials suggests the need for more refined and selective inclusion criteria.

In this context, we sought to include patients exhibiting multiple indicators suggestive of covert AF, including embolic ischemic patterns on MRI as imaging markers, LA enlargement and E/e′ ratio as echocardiographic markers, and elevated NT-proBNP levels as serum markers. These multimodal biomarkers aim to enhance the detection of hidden AF.

In contrast to previous studies, the present trial uniquely explores early AF detection not only in patients with ESUS, but also in those with LAA and SVO. By addressing a key unmet need in identifying covert AF, this study has the potential to significantly influence strategies for secondary stroke prevention.

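### Section 2.10 assigns paired tests to baseline variables, but patient characteristics have one value per patient, so these tests cannot examine the relationships named

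*Protocol article*

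**What the plan says.** The protocol article, Section 2.10 (Statistical Analysis), opens with the baseline variables: "For baseline variables, bivariate relationships will be examined by employing McNemar’s test for categorical variables and paired samples" t-tests or the "Wilcoxon signed-rank test for continuous variables, presented as either means with standard deviations or medians with interquartile ranges, depending on their distribution". It then gives McNemar's test for the primary outcome, with a risk difference and confidence interval, and adds: "This approach directly reflects the open-label paired design of the trial".

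Other sections show what is paired. Section 2.7 (Concomitant Application) says that at baseline "AF detection rates are concurrently compared using a single-lead wearable patch and a 24 h Holter monitor". Section 2.4 (Study Population) makes both recordings a condition of eligibility: "at least 18 h of recording on 24 h Holter monitoring" and "at least 72 h of recording on a single-lead wearable patch". The two devices are two readings on one cohort.

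The markers appear in three places. The Introduction says "we aim to explore the detection rates of incidental AF in patients exhibiting LA enlargement or elevated NT-proBNP levels", and calls these potential indicators of AF. Section 2.2 and the Discussion add E/e′ and the embolic imaging pattern; the Discussion says of the set: "These multimodal biomarkers aim to enhance the detection of hidden AF".

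**The concern.** McNemar, paired t and Wilcoxon signed-rank tests all need two measurements of the same quantity on the same unit. In this design AF detection has that structure, because each patient has a patch result and a Holter result. A patient's age, sex, LA size, E/e′ or NT-proBNP does not: it is the same value whichever device is being read.

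The relationships of interest for such variables lie between patients, chiefly between those in whom AF is detected and those in whom it is not. These are different people in groups of unequal size, and no matching is described.

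An analyst who follows the sentence literally has three options: report nothing from the tests, pair unrelated patients arbitrarily, or choose other tests after the data are in. The last is the likely outcome, and it leaves the published plan without force for this part of the analysis.

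**Working it through.** The plan states no figure to reproduce here. The check is whether each named test fits the data.

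**Inputs.** Tests: Section 2.10. One cohort with both devices: Sections 2.4 and 2.7. Enrolment 116, and planning detection rates of 2.8% (standard) and 15.8% (continuous monitoring): Section 2.9. Assumption: baseline variables means patient characteristics recorded once, since Section 2.10 gives no list.

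**Reading 1: patch against Holter.** Patient i has value x_i under both devices, so d_i = x_i − x_i = 0 for all 116.

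- Paired t: mean(d) / (SD(d)/√n) = 0 / (0/√116) = 0/0, undefined.
- Wilcoxon signed-rank: only non-zero differences are ranked. There are none, so the statistic is 0 and its p-value is undefined.
- McNemar, asymptotic: (b − c)²/(b + c) with b = c = 0 gives 0/0, undefined.
- McNemar, exact: binomial with b + c = 0 trials, so p = 1 whatever the data.

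Running the tests on 116 simulated patients with one LA size each (assumed mean 42 mm, SD 6 mm; dichotomised at 44 mm, giving 36 and 80) returned these results: no value for the paired t (115 degrees of freedom), no p-value for Wilcoxon or asymptotic McNemar, and p = 1 for exact McNemar.

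**Reading 2: AF detected against AF not detected.** The documents do not give the number with AF, so the planning rates serve as a range, applied to all enrolled for illustration only.

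- At 15.8%: 0.158 × 116 = 18.3, so about 18 and 98 patients.
- At 2.8%: 0.028 × 116 = 3.2, so about 3 and 113 patients.

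In neither case do pairs exist, and none of the three tests can be applied.

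**Reading 3: marker against AF within a patient.** McNemar can be computed on a table of LA enlargement (yes/no) by AF (yes/no). Its numerator b − c is the number of marker-positive patients minus the number of AF-positive patients, whatever the overlap. It tests whether the two are equally common, not whether they are associated.

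**What a suitable comparison could show.** For two independent groups, two-sided 5% and 80% power, the detectable standardised difference is (1.96 + 0.8416) × √(1/n₁ + 1/n₀), by normal approximation:

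- 18 and 98: 2.8016 × √(1/18 + 1/98) = 2.8016 × 0.2564 = 0.72.
- 3 and 113: 2.8016 × √(1/3 + 1/113) = 2.8016 × 0.585 = 1.64 (rough, with so few events).

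Only large differences would be found, and fewer patients are available within ESUS alone.

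**The case against.** **The variables could be device outputs.** Section 2.10 lists no baseline variables. Section 2.6 names outputs of the patch, such as average heart rate and premature contractions. If the Holter yields the same items, which the article does not say, paired tests on them would be valid. That holds for such quantities, but the sentence does not restrict itself to them. If this was the intent, it still needs rewording.

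**The marker aim is modest.** A reader might infer that the plan leaves a stated aim of relating LA size, E/e′ and NT-proBNP to AF without any analysis. The documents do not support this. The Introduction speaks of exploring detection rates in patients with LA enlargement or raised NT-proBNP and does not mention E/e′. Section 2.2 and the Discussion present the markers mainly as selection indicators. No outcome in Section 3 is a marker association. A detection rate in a marker-positive group needs only a proportion. What stands is narrower: no test named in Section 2.10 can support a claim that a marker indicates AF.

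**The analysis plan is not shown.** It may add a marker analysis, so the absence of one is not the point. The point is that the article names tests that do not fit.

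**A wider failure might be inferred.** It would be wrong to say that the baseline analysis yields nothing, or that every test is undefined. Descriptive summaries are already planned, and exact McNemar does return a value, though an uninformative one. McNemar for the primary outcome is appropriate.

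**Conclusion.** The sentence is wrong as written for patient characteristics. Against the device, the paired tests are degenerate; against AF status, they have no pairs; applied to a marker and AF in the same patient, McNemar answers a different question. This rests on baseline variables including characteristics recorded once per patient, which is the ordinary meaning of the term.

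The consequence is limited. No primary, secondary or tertiary outcome depends on these tests, and the sample size is not involved. What is lost is a usable, pre-stated method for the exploratory marker question. The group sizes of about 18 and 98 are illustrative, not predicted. The correction should be made because the stated method cannot be followed.

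**What to change.** Reword the first sentence of Section 2.10 to say that:

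- baseline characteristics are summarised once for the cohort, without paired tests;
- McNemar and paired t or signed-rank tests are reserved for quantities measured by both devices or at both visits;
- where AF-detected and AF-not-detected patients are compared on baseline markers, independent-sample methods are used (Fisher or chi-square; t-test or Mann-Whitney; or exact or penalised logistic regression with few covariates), labelled exploratory;
- these comparisons are run within ESUS or stratified by stroke subtype, and LA size is not tested between ESUS and LAA/SVO. Section 2.4 makes LA enlargement the condition for including LAA and small-vessel patients, so that contrast would partly reflect the entry rule, and a pooled model would mix selected with unselected patients.

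The cost is a few lines of text, with no change to data collection, sample size or the primary analysis. The small downside is that AF events will be few, so marker estimates will be imprecise and should be reported with confidence intervals.

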### 2.8. Clinical Monitoring

During the 6-month follow-up period, both AF detection rates and the occurrence of recurrent stroke will be evaluated. Recurrent stroke will be confirmed by brain MRI or CT imaging.

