### Study Limitations

This study has several limitations. First, it is not a randomized controlled trial, but rather a non-blinded, prospective observational study; therefore, the possibility of detection bias cannot be excluded. Second, the accuracy and completeness of measurements largely depend on patient cooperation. Third, the relatively short follow-up period of six months may underestimate the rates of AF diagnosis and recurrent stroke incidence. Fourth, patients with ESUS will undergo follow-up evaluations at enrollment (visit 0) and at 6 months (visit 1). The 6-month interval may be too long, potentially resulting in missed episodes of paroxysmal AF (pAF). However, a recent meta-analysis of randomized controlled trials (RCTs) conducted between 2012 and 2023 investigating new AF detection after ischemic stroke (IS), and transient ischemic attack (TIA) identified two statistically significant time windows for new AF detection: 0–14 days and 6–12 months [26].

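### The planned log-rank comparison between devices ignores that both devices are worn by the same patients, and its 12-month period contradicts the 6-month follow-up

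*Protocol article*

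**What the plan says.** Section 2.10 has two consecutive paragraphs on comparing the devices.

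- The first analyses the primary outcome "between the single-lead monitoring group and the control arm using McNemar’s test for paired binary outcomes", with a risk difference and 95% confidence interval from the discordant pairs. It adds: "This approach directly reflects the open-label paired design of the trial".
- The second says: "During the 12-month observation period, Kaplan–Meier curves will be generated for each arm and compared using a log-rank test". It does not name the event that the curves describe.

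Other sections show what the arms are and how long patients are followed.

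- Section 2.4 requires of each participant "at least 18 h of recording on 24 h Holter monitoring" and also at least 72 h of patch recording.
- Section 2.7 says that "AF detection rates are concurrently compared using a single-lead wearable patch and a 24 h Holter monitor". It schedules both devices twice in ESUS patients, at enrolment (V0) and at 6 months (V1).
- Section 2.8: "During the 6-month follow-up period, both AF detection rates and the occurrence of recurrent stroke will be evaluated".
- Section 3 defines the primary outcome over a 6-month follow-up made up of V0 and V1.
- The Limitations say that "the relatively short follow-up period of six months may underestimate the rates of AF diagnosis and recurrent stroke incidence".

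**The concern.** Two things conflict with the rest of the article, and a third makes the analysis of little use.

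1. **Pairing.** The log-rank variance is that of two independent samples. Here the two curves are two readings on one set of patients, as the preceding paragraph of section 2.10 acknowledges.
2. **Duration.** Section 2.10 alone gives an observation period of 12 months. No visit or recording is scheduled after V1.
3. **Time axis.** The devices look for AF only in two short windows, so a device-detection curve has essentially two steps, placed by the visit calendar. It adds little to the paired proportions.

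At stake is a second p-value for the same device contrast. It comes from a test that does not match the design, and it can fall on the other side of 0.05 from the McNemar result. The time axis would also suggest follow-up that the study does not have.

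**Working it through.** The plan gives no figure for this analysis, so there is none to reproduce. The check has three parts.

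**1. Follow-up.** Sections 2.8 and 3 and the Limitations say 6 months, and section 2.7 places the last device recording at 6 months. Section 2.10 says 12 months. The only other 6-to-12-month figure is in the Limitations, where it is a detection window from a cited meta-analysis and not this trial's schedule. Months 6 to 12 therefore have no scheduled data.

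**2. What ignoring the pairing does.** Take one look at N patients. Let a be the number detected by both devices, b by the patch only and c by Holter only. The log-rank test sees 2N independent records with d = 2a + b + c events.

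- Observed minus expected for the patch: (a + b) − d/2 = (b − c)/2.
- Log-rank variance: (d/4) × (2N − d)/(2N − 1).
- Log-rank chi-square: (b − c)² / [(2a + b + c) × (2N − d)/(2N − 1)].
- McNemar chi-square: (b − c)² / (b + c).

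The numerators are the same. The log-rank denominator also carries 2a, the concordant detections, which say nothing about a difference between devices. The more often the devices agree, the more the log-rank statistic shrinks. If they detect independently, the two denominators are about equal.

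*Example (assumed: N = 80, patch 9, Holter 3, all Holter detections also found by the patch, so a = 3, b = 6, c = 0).*

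- Log-rank: d = 12, observed 9, expected 6, variance 3 × 148/159 = 2.79. Chi-square 9/2.79 = 3.22, p = 0.073.
- Splitting the detections over the visits (patch 6 + 3, Holter 2 + 1): expected 4 + 4 × 74/152 = 5.95, variance 1.91 + 0.98 = 2.89. Chi-square 3.05²/2.89 = 3.22, again p = 0.073.
- Exact McNemar: 2 × 0.5⁶ = 0.031.

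**3. Size under assumed agreement.** The article gives no agreement between devices and no number of ESUS patients, so these are ranges. AF is looked for at V0 and V1 only.

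*Equal devices (null), each detecting 8% per visit, 80 pairs, nominal 5%:*

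| Detected by both, per visit | Log-rank rejects |
|---|---|
| 6% | under 0.1% |
| 4% | about 1% |
| 2% | about 2.5 to 3% |
| 1% | about 4.5% |

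With 55 and 116 pairs the high-agreement row is again about 0 to 0.1%. Exact McNemar is also conservative here, at 1.0% to 3.1% over the same four rows. Asymptotic McNemar stays near nominal: in the high-agreement row it is 3.8% with 55 pairs and 4.9% with 116.

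*Power, Holter detections assumed nested in patch detections:*

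| Cumulative detection | Pairs | Log-rank | Exact McNemar | Asymptotic McNemar |
|---|---|---|---|---|
| 15.8% vs 2.8% (rates in section 2.9) | 55 | 74% | 73% | 94% |
| 15.8% vs 2.8% | 116 | 99% | 99.7% | 100% |
| about 16% vs 8% (assumed) | 55 | 12% | 27% | 65% |
| about 16% vs 8% (assumed) | 116 | 42% | 91% | 99% |

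**The case against.** The strongest reply is that this is a supporting analysis. The primary outcome has its own paired test and interval, and no stated conclusion rests on the Kaplan–Meier sentence. With positively correlated readings the error cannot manufacture a false claim for the patch. At the planning rates with 116 pairs, the log-rank test loses almost nothing, and with 55 pairs it matches exact McNemar. All of this stands, and it limits the severity.

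Two readings might rescue the text. Arm could mean ESUS against LAA/SVO, which would be independent groups, but section 2.10 uses the word for the device contrast and section 3 restricts recurrent stroke to ESUS. Twelve months could mean up to 6 months from stroke to entry plus 6 months of follow-up, but the article nowhere says so.

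A reader might also infer more than the article supports.

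- **That recurrent stroke will be compared by device.** Those curves would coincide, since the patients and events are the same. But the event is unnamed, and nothing says stroke will be split by device.
- **That two-step curves are themselves invalid.** With a variance that respects the pairing they would be uninformative, not wrong.
- **That the log-rank test must conflict with McNemar.** It can, as in the example. That is one constructed case.

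**Conclusion.** Section 2.10 is wrong as written on two counts: an independent-groups test is applied to paired readings, and a 12-month period contradicts the 6-month follow-up stated elsewhere. It should be fixed, but it does not undermine the trial.

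The error lies towards too few rejections. Under the null with 55 to 116 pairs, the nominal 5% log-rank test rejects in about 0% (high agreement) to nearly 5% (devices almost independent). The loss of power ranges from negligible at 15.8% vs 2.8% with 116 pairs to severe at about 16% vs 8%. It would be too strong to say that the primary result is compromised or the false-positive rate inflated: the McNemar analysis is untouched.

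The algebra and the contradiction in duration need no assumptions. The sizes rest on assumed agreement patterns and assumed pair counts. The 116 recruited is the total, patients with LAA or SVO strokes are also enrolled, and the article does not give the ESUS number.

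**What to change.** In section 2.10:

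1. Delete the log-rank test between devices. Compare the devices by McNemar's test and the paired risk difference with 95% CI, at V0 and at V0 and V1 combined.
2. Reconcile the 12-month period with the 6-month follow-up in sections 2.8 and 3 and the Limitations.
3. If a Kaplan–Meier curve is kept, name its event and show it for a single cohort up to the 6-month visit, without a between-device test. Recurrent stroke in ESUS patients is one example.

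The cost is about two sentences and less analysis than planned. Recruitment has ended, but the change needs no new data and does not alter the primary analysis.

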## 3. Study Outcomes

The primary outcome was the detection of AF using a single-lead wearable patch compared to a 24 h Holter monitor during the 6-month follow-up period (baseline visit: V0; 6-month visit: V1) in patients with ESUS. The secondary outcome was the comparison of AF detection rates between the two monitoring devices in stroke patients with large artery atherosclerosis (LAA) or small-vessel occlusion (SVO). The tertiary outcome was the occurrence of recurrent stroke among patients with ESUS, given that AF is infrequently diagnosed in individuals who experience multiple recurrent ESUS events (Figure 1).

